### **3 STUDY DESIGN**

#### **3.1 Type of study**

This study is an International, multi-centre, prospective, controlled RCT using a 2x2 factorial design; involving a surgical intervention and a pharmacological intervention. For the surgical intervention, surgeons will be unblinded while patients, care providers, data collectors and outcome adjudicators will be blinded. For the pharmacologic intervention, patients, all care providers, data collectors and outcome adjudicators will be blinded. Approximately 10 Canadian and 40 International centers will participate.

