| 
Study Drug(s) or Intervention(s)
                                      | 
Each patient will be randomized to a SVG harvested in the conventional fashion (open or endoscopic) or using the no touch technique (single-blinded). The pharmacological arm of the factorial design will also have patients randomized to fish-oil or placebo (double-blinded) which will be started preoperatively and continued for 1 year postoperatively.
                                                                                                                                                                                                                                                                                                                                                                                                                                                                                                                                                                                                                                                                                                                                                                                                                                                                                                                                                                                                                                                                                                                                                                                                                                                                                                                                                                                                                                                                                                                                                                                                                                                                                       |

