### **3.3 Method of treatment allocation**

Prior to the trial, all surgeons will be provided with a copy of the trial protocol. Research personnel will screen patients in the preoperative assessment clinic to identify patients who fulfill the eligibility criteria. The personnel will also review the daily surgical list for eligible in-patients. Patients who fulfill the eligibility criteria will be approached for informed consent. Eligible and consenting patients will be randomized by calling a 24 hour interactive voice response system (IVRS) or by logging-in to a web-based randomization service. Treatment allocation to either “no touch” or conventional SVG harvesting, and fish-oil supplementation or placebo will be performed according to a computer generated randomization list. This will be stratified by site using a factorial design; blocked randomization will be performed with randomly sized blocks to maintain concealment. Randomization will also be stratified according to the control technique (open vs. endoscopic) to minimize bias following the pilot phase. Patients will be considered as randomized as soon as the treatment allocation is given over the telephone.

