## **5 STUDY PROCEDURES**

### **5.1 Treatments**

#### **A. SURGICAL ARM**

Eligible patients undergoing multi-vessel CABG with ≥1 SVG, will have the study SVG directed to the most important coronary target intended for a venous conduit. **In the experimental arm**, patients will be randomized to have the study SVG harvested from their lower leg using the novel, pedicled, atraumatic **“no touch” technique** (45-48). **In the control group**, patients will have their study SVG graft harvested in a **conventional fashion** without a pedicle.

The atraumatic “no touch” approach involves a longitudinal incision in the lower leg below the knee to the medial malleolus. However, the SVG is harvested with its surrounding tissue (pedicled). It is not manually dilated; it is left *in situ* until required and allowed to dilate when exposed to arterial pressure. All study patients will undergo duplex scanning and mapping of the saphenous veins preoperatively, to assess the quality of the vein as well as limit the creation of flaps during the vein dissection. Saphenous veins will be harvested from the thigh in the event that the lower leg vein is of poor quality or small size, or in patients with marked edema or peripheral vascular disease with concerns regarding wound healing.

The conventional approach involves a longitudinal incision in the lower leg, just below the knee to the medial malleolus. The vein is identified and the adventitial layer is stripped to directly expose and visualize the SV and its branches. Vein from the thigh may be harvested for similar reasons as

discussed above. It is then excised and distended using heparinized saline. It is standard practice in many institutions to harvest SV using an endoscopic, minimally invasive rather than an open approach, for reasons of improved cosmesis and because local wound complications are reduced (70). For relevance and to reflect contemporary trends in practice, the control group/conventional approach may include the minimally harvested SVG, which is otherwise prepared in a similar manner, i.e. stripped of adventitia and manually distended, albeit through a smaller incision. A recent observational study of a large multi-centre sample (50) and post hoc secondary analysis from the large multi-centre PREVENT IV RCT (5) reported poorer patency and clinical outcomes using endoscopically harvested SVG, however, institutions that predominantly employ endoscopic harvesting may continue to choose this technique.

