### 5.4 Encouraging compliance

Noncompliance is not expected to be a major issue in this trial. The interventions are simple and the surgical intervention occurs at a single time-point and is controlled by the treating physician,

outcomes are objective, and data-forms are concise. Patient compliance to the study supplements will be monitored at follow-up visits via pill counts.

Patients are generally followed by their surgeons/cardiologists for several years after their procedure, and it is expected 99.9% follow-up at one month and over 99% follow-up at 6 months will be obtained. PHRI has substantial experience in documenting vital status in >99.5% in its clinical trials involving over 200,000 subjects recruited from over 50 countries and followed for up to 8 years. This expectation will be met in this study, especially with a post-surgical population in whom clinical follow-up by the surgeon for a minimum of 3 months is generally routine.

The overall study has been designed such that only one SVG is required to facilitate recruitment. We did consider restricting the study to patients who required at least 2 SVGs, as the event rates would presumably be greater. The chosen protocol does allow patients who are having only 2 grafts constructed (ITA and 1 SVG) and is compatible with patients undergoing more extensive arterial revascularization. We anticipate that the average number of vein grafts/patient will be 1.5 (as in GRIIP) (6). We considered restricting the control group to open harvesting rather than allow for endoscopic harvesting to be performed as well. We thought it important to include endoscopic harvesting as it is a commonly used technique, and there is recent evidence that endoscopic vein harvesting purports worse patency and clinical outcomes than conventional SVG harvesting (50). Although endoscopic patients will usually be unblinded, endpoint adjudication is blinded. Our post-hoc analysis will also aim to elucidate any difference in graft patency in the control SVGs harvested in the conventional open versus endoscopic techniques. We expect that the RRR will be similar or greater comparing endoscopic and no-touch versus open control and no-touch.

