## **8 STATISTICAL CONSIDERATIONS**

### **8.1 Study outcomes**

The aim of this study for the **Surgical Arm** is to determine whether the “no touch” technique results in a lower proportion of study SVGs that are totally (100%) occluded on 1-year post-CABG angiography, compared to conventional SVG harvesting techniques, and death due to cardiovascular or unknown causes. The aim for this study for the **Pharmacological Arm** is to determine whether N-3 polyunsaturated fatty acid (fish oil) oral supplementation results in a lower proportion of patients with  $\geq 1$  graft (study SVG, non-study SVG or arterial graft) totally (100%) occluded at 1-year post-CABG angiography, compared to those who received placebo. These events will be adjudicated, as defined in the operations manual.

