### **9.3 Event Adjudication Committee**

The Events Adjudication Committee will blindly evaluate all primary outcome events using standardized definitions, along with supporting documentation. Members of the Events Adjudication Committee will be chosen based on their clinical expertise. All event adjudication will be blinded to treatment group.

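### Section 3.1 calls patients, care providers and data collectors blinded to harvest technique, but Section 5.4 concedes that endoscopic patients usually are not, and no blinded assessment is stated for the harvest-site and quality-of-life outcomes

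*Protocol*

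**What the plan says.** Section 3.1 sets out blinding for the surgical intervention in one clause: "surgeons will be unblinded while patients, care providers, data collectors and outcome adjudicators will be blinded". The synopsis, under study interventions, labels the same comparison more briefly, "using the no touch technique (single-blinded", without saying who is blind.

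Section 5.1 permits two control techniques: "the control group/conventional approach may include the minimally harvested SVG". It describes the no-touch and open conventional harvests as using much the same long lower-leg incision, and the endoscopic harvest as using a smaller one.

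Section 5.4 explains why endoscopic control was allowed and accepts a consequence: "Although endoscopic patients will usually be unblinded, endpoint adjudication is blinded".

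On adjudication, Section 9.3 says: "The Events Adjudication Committee will blindly evaluate all primary outcome events using standardized definitions", and adds: "All event adjudication will be blinded to treatment group". Section 8.1, directly after stating the two primary aims, says: "These events will be adjudicated, as defined in the operations manual".

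Section 2 has a secondary objective that harvest-site events (infection, haematoma, swelling, neuropathy) and quality of life at 1 year are similar between the surgical groups. Section 5.5 lists the four harvest-site events as a secondary outcome. Table 1 places leg-wound assessment at 30 days, 3 months and 1 year, and the quality-of-life questionnaire at baseline, 30 days and 1 year.

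**The concern.** The blinding statement in Section 3.1 is a design property that readers of the eventual report will rely on. By the protocol's own account it fails for some patients, and the section that admits this points to a safeguard that, as written, does not cover the outcomes most open to expectation.

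Swelling, neuropathy, parts of the infection assessment and quality of life depend on what the patient reports and what the examiner judges. Expectations may not be neutral either: Section 5.1 gives better cosmesis and fewer wound problems as reasons why centres harvest endoscopically. The objective for these outcomes is similarity, so a shift in reporting in either direction bears on the conclusion. If the endoscopic-control and open-control parts of the trial are pooled and Section 3.1 is taken at face value, the harvest-site comparison will look more protected than it is.

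**Working it through.** The protocol gives no figure on this point, so the check sets the statements side by side.

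**1. Patients.** Section 3.1: blinded, no exception. Section 5.4: usually not blinded when the harvest is endoscopic. These conflict directly. The conflict is not confined to the control arm: at a site whose control technique is endoscopic, a long incision points to no-touch as plainly as a short one points to control.

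**2. Care providers and data collectors.** Section 3.1: blinded. Section 5.4 is silent. Section 5.1 gives the two techniques visibly different incisions, and Section 5.2 has the leg examined at three visits. Anyone who examines the leg and knows the site's control technique can probably tell the arm. This is inferred. The cue is also imperfect, since Section 5.1 allows thigh harvest under both approaches.

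**3. Scope of adjudication.** Section 9.3 names primary outcome events. Its closing sentence says that whatever is adjudicated is adjudicated blind; it adds no outcomes to the list. Section 8.1 mentions adjudication only after the primary aims. The word *only* is a reading of these two sections, and the operations manual could widen the scope.

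**4. What is left without cover.**

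| Outcome | Who observes it | Blinded assessment stated? |
|---|---|---|
| Primary (total occlusion; cardiovascular or unknown-cause death) | CT reading and adjudication committee | Yes (9.3) |
| Harvest-site infection, haematoma, swelling, neuropathy | Leg-wound assessor and patient | None beyond 3.1 |
| Quality of life | Patient | None beyond 3.1 |

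For the last two rows Section 3.1 is the only protection offered, and step 1 shows that it does not hold for patients where control is endoscopic. Section 8.3 plans t tests on harvest-site infection scores and chi-square or Fisher tests on harvest-site complications, and names no blinded assessor.

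**5. Can the design separate the two situations?** Largely. Section 3.3 says: "Randomization will also be stratified according to the control technique (open vs. endoscopic", and ties this to the period after the pilot. A stratum defined by intended control technique applies to both arms and is fixed before allocation, so the arms are comparable within it. In the open-control stratum the incisions are similar, so blinding is feasible. Section 8.5 keeps the pilot patients in the final analysis: 50 of 1,550, or 50 / 1,550 = 3.2%, may carry no such stratum. Open versus endoscopic harvest already appears in Section 5.4 (a post hoc look at control-graft patency) and Section 8.3 (a covariate for occlusion), but not for harvest-site outcomes.

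**6. Size.** The protocol does not state the share of patients at endoscopic-control sites, so no count follows. The contradiction exists at any share above zero.

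**The case against.** The strongest reply is that this is a disclosed trade-off. Section 5.4 says that restriction to open control was considered, explains why it was rejected, and admits the unblinding. On that view all that remains is one sentence in Section 3.1 that was not brought into line. This is fair as to intent. It does not supply blinded assessment for the harvest-site outcomes, and Section 5.4 offers adjudication as the answer without noting how far adjudication reaches.

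Three stronger readings are tempting and are not supported.

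- A reader might infer that blinding is wholly absent where control is endoscopic. Section 5.4 withdraws it for patients only, and only usually; adjudicators stay blind. Unblinding of wound assessors is a reasonable inference, not a stated fact.
- A reader might infer that the primary outcome is biased, because patients decide whether to attend the scan and clinically directed angiograms count (Section 5.5). Section 8.5 does expect 20% to miss the scan, 0.20 × 1,550 = 310 patients, and in the earlier radial-artery trial it cites, 77 of 121 listed reasons (77 + 17 + 19 + 8), about 64%, were withdrawal of consent. That shows a possible route. Nothing in the document shows that attendance or angiography differs by arm, or in which direction, and the events themselves are adjudicated blind.
- A reader might treat a difference between strata as the size of the unblinding bias. It is not: endoscopic harvest may itself change wound outcomes, so such a difference mixes technique effect with assessment bias.

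It is also true that detailed tables by stratum often belong in the statistical analysis plan. Who is blinded does not; that is for the protocol to state correctly.

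**Conclusion.** Section 3.1 is wrong as written for patients at endoscopic-control sites, on the protocol's own admission, and probably for those who assess their leg wounds. The harvest-site and quality-of-life outcomes in the secondary objective have no stated blinded assessment there. This should be corrected, but it does not undermine the primary surgical comparison.

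The conclusion rests on two assumptions: that the operations manual does not extend blinded adjudication or assessment to the harvest-site outcomes, and that incision length is usually recognisable at the wound visits. If the manual does extend it, the harvest-site part falls away and the conflict between Sections 3.1 and 5.4 remains. Neither the number of patients affected nor the size of any bias can be derived from the protocol.

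**What to change.** 1. Reconcile Section 3.1 and the synopsis label with Section 5.4: state that patients, and probably leg-wound assessors, are not reliably blinded where the control technique is endoscopic. State in Section 9.3 whether any harvest-site outcome is assessed or adjudicated blind.
2. Report harvest-site and quality-of-life comparisons by arm within control-technique stratum (open, endoscopic) alongside the pooled result, naming the open stratum as the comparison in which blinding is feasible. Define the stratum by intended control technique, not by the harvest performed, so that no-touch patients are classified too.
3. Classify the 50 pilot patients by their site's intended control technique, or show them separately.
4. Say in the text that differences between strata do not measure unblinding bias.
5. Optionally, tabulate scan completion and clinically directed angiography by arm within stratum, as a check only.

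No extra assessor, visit or change to treatment is needed. The cost is wording, a few tables and wider intervals: with similar event rates, a stratum holding a fraction f of the patients has a standard error about 1/√f times the pooled one.

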### **3.2 Expected number of subjects**

We expect to recruit 50 patients within the pilot phase. This is a convenience sample size to give us enough experience to assess our pilot objectives in support of a 1,550 patient study. The sample size for the full study is approximately 387 patients per group; for a total of 1,550 patients.

### **3.3 Method of treatment allocation**

Prior to the trial, all surgeons will be provided with a copy of the trial protocol. Research personnel will screen patients in the preoperative assessment clinic to identify patients who fulfill the eligibility criteria. The personnel will also review the daily surgical list for eligible in-patients. Patients who fulfill the eligibility criteria will be approached for informed consent. Eligible and consenting patients will be randomized by calling a 24 hour interactive voice response system (IVRS) or by logging-in to a web-based randomization service. Treatment allocation to either “no touch” or conventional SVG harvesting, and fish-oil supplementation or placebo will be performed according to a computer generated randomization list. This will be stratified by site using a factorial design; blocked randomization will be performed with randomly sized blocks to maintain concealment. Randomization will also be stratified according to the control technique (open vs. endoscopic) to minimize bias following the pilot phase. Patients will be considered as randomized as soon as the treatment allocation is given over the telephone.

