## **B. PHARMACOLOGICAL ARM**

Patients will be randomized to receive either fish-oil oral supplements (Ocean Nutrition, Dartmouth, NS) or a colour and taste-matched placebo (Ocean Nutrition, Dartmouth, NS). Upon randomization at the time of accepting referral for surgery and consent, the subjects will consume two 1g tablets, daily (as used in prior clinical trials) for 1 year. Study supplements will not be administered on the day of surgery. The duration of preoperative therapy is not mandated but will be evaluated post hoc; surgery should occur within 30 days of randomization. In the event that the patient misses any dose(s) of study supplement, patients will be instructed to resume the next scheduled study dose and discouraged from taking more than two study supplements per day.

Postoperative medical management using aspirin and/or other antithrombotic agents, statins, beta blockers and/or ACE-inhibitors will be prescribed in a standardized fashion according to published STS and AHA/ACC guidelines.

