## **6 SUPPLEMENT SUPPLIES**

### **6.1 Study Supplements**

Patients will receive either fish oil supplements or placebo to be taken twice daily for 1 year post-CABG. Patients will start taking the supplements as soon as they consent and are randomized until their surgery (study supplements not to be administered on day of surgery), and will commence again postoperatively as soon as they are able to take oral medications. The fish oil supplement (Omega Pure 40/20 EE 1000 mg capsules – containing 340 mg eicosapentaenoic acid (EHA) and 170 mg docosahexaenoic acid (DHA)) and placebo (50/50 corn/soybean placebo 1000 mg capsules) will be obtained from Ocean Nutrition Canada. Fish oils or placebo will be given to the patient by the Study Nurse. Patients will receive a bottle containing 185 pills (enough for 3 months) when they are discharged, another bottle at the 3, 6 and 9 month follow-up visits.

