### **8.2 Analysis population**

The main analysis will be by an intention-to-treat approach (i.e., all randomized patients in the study will be included in the analysis). At least 1,550 patients will be equally allocated to the four treatment groups.

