### B. PHARMACOLOGICAL ARM

The literature suggests that fish-oils provide a RRR of about 25% compared to placebo (54,55, 65,69). Given a two-tailed alpha of 0.05, and an estimated 30% of control patients with  $\geq 1$  graft occluded at 1-year, a sample of 540 patients in each group (fish-oil versus placebo) will provide a power of 80% to detect a RRR of 25%. A sample size of 615 patients (required for the surgical intervention) provides approximately 85% power to test the fish oil hypothesis (see Table 2b).

We anticipate that 80% of patients will undergo 1-year coronary CT angiography, which is consistent with our past trial experience (7). The primary reason that patients failed to undergo late angiography in RAPS was late withdrawal of consent in 77 patients, protocol violation in 17 patients, new contraindication precluding research angiography in 19 patients and death in 8 patients (7). To adjust for this potential loss to follow-up angiography, the corrected sample size is 769 patients in each surgical group to ensure adequate statistical power when making our conclusions for both arms of the factorial design. Thus we aim to recruit a **total of 1,550** patients for the overall study across ~50 participating sites, 10 Canadian and the remaining International. The pilot phase will recruit 50 patients from 10 sites (5 Canadian and 5 International). Pilot patients will be included in the final analysis. *While MACE between groups will be tested using the total sample size, we will only be able to detect very large differences at 1 year, as MACE is expected to be approximately 10 - 12% (6,7,17).*

**Table 2a:** Sample Size Estimates for Primary Endpoint (Surgical Arm) – 1-Year Graft Occlusion (two-tailed  $\alpha=0.05$ ,  $\beta=0.20$ )

| Control Event Rate | Relative Risk Reduction |             |                     |             |                     |             |                     |             |                     |             |
|--------------------|-------------------------|-------------|---------------------|-------------|---------------------|-------------|---------------------|-------------|---------------------|-------------|
|                    | 20%                     |             | 25%                 |             | 30%                 |             | 35%                 |             | 40%                 |             |

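### The harvest allocation is released with the supplement allocation at consent, so some patients in the surgical intention-to-treat set may never have a study graft, and the surgeon knows the arm before the conduits are final

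*Protocol*

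**What the plan says.** Protocol section 3.3 describes a single telephone or web transaction that assigns harvest technique "and fish-oil supplementation or placebo will be performed according to a computer generated randomization list". It then states: "Patients will be considered as randomized as soon as the treatment allocation is given over the telephone".

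Section 5.1 B places this step early: "Upon randomization at the time of accepting referral for surgery and consent". On the interval that follows it says "surgery should occur within 30 days of randomization". Section 6.1 explains the early timing for the supplement: "Patients will start taking the supplements as soon as they consent and are randomized until their surgery". Section 3.4, by contrast, describes harvest as an intervention confined to the operation itself.

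The entry criterion in section 4.1 concerns a planned vein graft, judged before surgery. Section 8.2 defines the main analysis as intention to treat, under which "all randomized patients in the study will be included in the analysis". Section 8.3 applies a chi-square test to study-graft occlusion on that principle, and section 5.5 defines the surgical primary outcome as the proportion of study vein grafts occluded, together with cardiovascular or unknown-cause death.

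On attrition, section 8.5 says: "We anticipate that 80% of patients will undergo 1-year coronary CT angiography". On blinding, section 3.1 says: "For the surgical intervention, surgeons will be unblinded". Nothing delays the harvest allocation to the day of surgery or says how a randomized patient without CABG or without a vein graft is counted.

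**The concern.** Only the supplement has to be assigned at consent, because only the supplement is used before surgery. Releasing the harvest code at the same moment has two consequences.

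First, the analysis set and the outcome do not match. Patients who die waiting, cancel, are treated another way or receive only arterial grafts are randomized for harvest but have no study graft. They must be either dropped after randomization or given an outcome by convention. A preoperative death from a cardiovascular or unknown cause could even count as an event in the harvest comparison although no vein was taken.

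Second, the unblinded surgeon knows the arm while the conduit plan is still open. Section 5.1 A leaves multiple arterial grafting to the surgeon's discretion. It asks for the study-graft target to be named before surgery, but not before the allocation is known. Whether a patient ends up with a study graft could therefore depend on the arm, and a larger sample would not cure that.

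**Working it through.** **Reproducing the plan's figure (section 8.5).** Inputs: 20% v 14%, two-sided alpha 0.05, power 80%; the mean rate is 0.17.

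n = [1.960 x sqrt(2 x 0.17 x 0.83) + 0.8416 x sqrt(0.20 x 0.80 + 0.14 x 0.86)]^2 / 0.06^2 = 614.1, so 615 per group. Then 615 / 0.80 = 768.75, so 769 per group, and 2 x 769 = 1,538, which the protocol rounds up to 1,550. The arithmetic is sound. The rounding leaves 1,550 - 1,538 = 12 patients in hand.

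**Starting power.** 1,550 / 2 = 775 per harvest group; 775 x 0.80 = 620 evaluable.

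Power = Phi{[0.06 x sqrt(620) - 1.960 x sqrt(0.2822)] / sqrt(0.2804)} = Phi(0.855) = 80.4%.

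**Patients without a study graft.** The documents give no rate, so a share q of 1-5% is an assumption: 1,550 x 0.01 = 15.5 to 1,550 x 0.05 = 77.5 patients. Dropped means n = 775 x 0.80 x (1 - q) per group at 20% v 14%. Kept as non-events means 620 per group with both rates multiplied by (1 - q), for example 19.0% v 13.3% at q = 5%.

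| q | n if dropped | Power, dropped | Power, non-events |
|---|---|---|---|
| 0% | 620 | 80.4% | 80.4% |
| 1% | 613.8 | 80.0% | 79.9% |
| 2% | 607.6 | 79.6% | 79.4% |
| 3% | 601.4 | 79.2% | 78.9% |
| 5% | 589 | 78.3% | 77.9% |

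Counting such patients as events in both groups would cost more (78.1% at 1%, 69.1% at 5%). The protocol does not suggest that rule; the figures only show that the counting convention matters more than the lost numbers.

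**Arm-dependent loss of the study graft, true null.** Assume that both techniques have 20% occlusion, and that a share a of no-touch patients, whose risk is r times 20%, receive no vein graft, with no such loss in the control arm. The observed no-touch rate is (0.20 - a x r x 0.20) / (1 - a). With a = 5% and r = 2 it is (0.20 - 0.02) / 0.95 = 18.9%. The table gives the chance of a significant result in favour of no-touch, with 620 control patients and 620 x (1 - a) no-touch patients; the nominal value is 2.5%.

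| a | r = 1 | r = 1.25 | r = 1.5 | r = 2 |
|---|---|---|---|---|
| 2% | 2.5% | 2.8% | 3.1% | 3.8% |
| 5% | 2.5% | 3.3% | 4.2% | 6.7% |
| 8% | 2.5% | 3.8% | 5.7% | 11.5% |

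The inflation needs both one-sided avoidance and higher risk in those avoided. With equal risk (r = 1) there is none.

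**The case against.** **The analysis set could be left to a SAP.** A SAP that is not shown may define a modified set for patients without a graft, and an outcome expressed per study graft already leaves them out of the graft denominator. This stands in part. But when the allocation is released is a protocol decision, and section 8.2 as written fixes everyone randomized. A later exclusion would act after the surgeon knew the arm.

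**The power loss is small and may be partly covered.** This stands. The 80% in section 8.5 is a share of all patients. The reasons it lists come from an earlier trial and include protocol violations, so some patients without a study graft may already be allowed for. A reader might infer that the sample size is wrong or the trial seriously underpowered; the documents do not support that.

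**The protocol limits the motive to avoid the vein in one arm.** A reader might infer that the surgical result will be biased. The documents do not show this. Open conventional and no-touch harvest use much the same lower-leg incision (5.1 A). Patients judged at excessive wound-infection risk are excluded beforehand (4.2). Vein mapping is mandatory, and thigh harvest is provided for poor leg vein or healing concerns. The contrast in incision arises mainly against endoscopic control, which becomes a stratum after the pilot (3.3). Nothing links avoidance to higher occlusion risk. The possibility remains; its size is assumed.

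**The interval is not a fixed 30 days.** This also stands. The wording is a target, and in-patients found on the daily list may be randomized close to surgery.

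A reader might also blame joint allocation for the unclear time origin of fish-oil deaths. That is a separate ambiguity: graft occlusion can only be timed from CABG, and delaying the harvest code would not settle when deaths start to count.

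**Conclusion.** The point holds as a design improvement. The harvest allocation is released earlier than harvest requires, so the surgical intention-to-treat set can contain patients for whom the surgical outcome cannot exist, and the arm is known before the conduits are final.

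If 1-5% are affected, the power cost is at most about 2.5 points (80.4% to 77.9%) when they are dropped or kept as non-events. The more serious risk, arm-dependent loss of the study graft, is plausible but undocumented. The range of about 2.8-11.5% for false claims of benefit rests wholly on assumed one-sided avoidance of 2-8% and an assumed risk ratio of 1.25-2; the upper end needs both at their extremes. It describes what the design leaves open and is not a forecast.

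**What to change.** Keep the randomization list, the strata and the supplement allocation as they are. Amend section 3.3 so that the IVRS or web system withholds the harvest code until just before surgery. It would release the code once the team has confirmed that CABG with at least one vein graft is going ahead and has recorded the planned conduits and the study-graft target.

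Amend section 8.2 so that the surgical intention-to-treat set, and the set for the interaction test, are the patients with a released harvest code. All patients randomized to supplement or placebo remain the fish-oil set.

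The cost is a second log-in, a few codes never released with slight imbalance between cells, and slightly different sets for the two factors. The remedy is partial: conduits can still change during the operation after release, so such changes should be reported by arm.
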